## Abstract

**Background:**

Informal caregivers of persons with dementia (PWD) often suffer adverse impacts on their mental health and require interventions for effective support. As they are often occupied with providing care, web-based interventions could be more convenient and efficient for them. However, there is currently a dearth of evidence-based mobile interventions to enhance the mental well-being of dementia caregivers locally, especially ones that are user-centered and culturally relevant. Hence, having designed an app based on feedback from local dementia caregivers, this study will evaluate the effectiveness of this mobile app in promoting the mental health of informal caregivers of PWD in Singapore.

**Methods:**

A pilot two-armed randomised controlled trial will be conducted on 60 informal caregivers of PWD recruited via convenience and snowball sampling. Thirty participants will be assigned to the intervention group, while another 30 will be in a waiting-list control group. Questionnaires will be administered at baseline and one month after, with the primary outcome being the difference in the change of depressive symptoms among the two groups.

**Statistical analysis:**

Primary analyses will follow the intention-to-treat principle and compare changes from baseline to the one-month follow-up time point relative to the control group. A repeated measures ANOVA will be conducted to examine differences between the groups over time.

**Significance:**

To our knowledge, this is the first study in Singapore that seeks to promote the mental health of informal dementia caregivers through a mobile-based intervention. The findings can inform the development and evaluation of future evidence-based digital interventions for local informal caregivers of PWD to address the gap in availability of such resources for them.

**Trial registration:**

ClinicalTrials.gov (NCT05551533). Registration date: September 22, 2022.

## Background

Based on a nationwide study conducted in 2013, approximately 10% of older adults above the age of 60 years suffer from dementia in Singapore [1], and this number will likely grow due to the rapidly ageing population [2]. With this, the cost of informal dementia care is also expected to rise [3] as more people will have to take on the role of caring for PWD living at home. As dementia progresses, PWD require high levels of care which is mostly provided by informal caregivers, usually family members of the PWD [4] who are often untrained for this highly demanding role [5].

As a result, informal dementia caregivers often face physical, financial, and social stressors which increase their risk of poor mental health outcomes [6]. The transactional model of stress and coping [7] is commonly used to understand this stress experienced by dementia caregivers [8]. The model posits that stress is a response experienced after a two-stage appraisal process by the individual. While the primary appraisal involves the interpretation of the stressor based on one’s background, past experiences, and personality, the secondary appraisal is the assessment of available coping resources and strategies to manage the stressor [9]. Accordingly, caregivers appraise a situation as stressful when the demands of the stressor exceed the available coping resources [10]. Consequently, this strain may manifest as emotional and psychological health outcomes such as psychological morbidity [4, 11].

High rates of caregiver burden and psychological morbidity (i.e., depression, anxiety) amongst informal dementia caregivers are well-documented in the extant literature. For instance, Connors et al. [12] found that 47.4% of caregivers of PWD had clinically significant levels of burden at baseline, with this proportion increasing to 56.8% after three years. Similarly, a recent meta-analysis reported a pooled prevalence of 49.3% and 31.2% amongst caregivers of PWD for burden and depression, respectively [13]. Likewise, a meta-analysis of 17 studies found that the aggregate prevalence of depression and anxiety amongst caregivers of patients with Alzheimer’s disease was 34.0% and 43.6% respectively [14]. In the Asian context, a 42.8% prevalence of depression was reported for a sample of caregivers of PWD in China [15], while 64.6% of a small sample of dementia caregivers in Hong Kong were clinically at risk for depression [16]. Taken together, the existing literature indicates significant rates of mental health concerns amongst informal dementia caregivers, which requires intervention.

### Protective factors for dementia caregiving

Certain protective factors have been shown to buffer negative outcomes for informal caregivers. Notably, prior research revealed that higher caregiving self-efficacy, which refers to the caregiver’s perception of their ability to perform caregiving tasks competently [17], is associated with lower levels of depressive symptoms [18] and mediates caregiver burden to improve psychological well-being [19]. Similarly, caregivers’ knowledge of dementia can help them build confidence in managing PWD, reducing caregiver burden and anxiety [20].

Another factor which could determine the extent of stress caregivers experience is coping strategies [21], with Lazarus and Folkman’s model [7] postulating that the type of coping strategy employed mediates the individual’s adaptation to stress. To elaborate, emotion-focused coping strategies have been shown to reduce caregiver anxiety, depression, burnout, and stress, while problem-focused coping strategies are linked to larger improvements in depressive symptoms, anxiety, and perceived stress [22]. Additionally, identifying the positive aspects of caregiving (PAC) is another protective factor for dementia caregiving, with a higher perceived PAC associated with fewer depressive symptoms and lower burden [23]. Overall, interventions to enhance these areas may help to protect the mental health of informal dementia caregivers.

### Mobile-based interventions

For informal caregivers who are largely occupied with caregiving duties, have transportation difficulties, or do not want to leave the PWD unattended, in-person interventions may be too time-consuming and burdensome [24]. For instance, informal caregivers of PWD in Singapore reported an average of 55 hours spent weekly on caregiving [25]. For this reason, the use of mobile devices in healthcare is beneficial as they are highly accessible, personal, and cost-effective [26, 27]. In addition, access to smartphones has become increasingly widespread, with 97% of Singapore residents owning a smartphone [28]. Furthermore, local caregivers of PWD in our prior study expressed interest and receptivity towards using digital health interventions provided they include helpful features to assist them in caring for PWD or enhancing their well-being [29]. Some of these functions mentioned by caregivers of PWD in the study include knowledge on dementia, caring for PWD, and self-care, and a list of resources [29]. In view of these, there is immense potential for mobile interventions to be a more viable way of supporting informal caregivers in the local setting. In fact, there has already been a proliferation of mobile health interventions in Western countries due to their convenience, privacy-preserving delivery, and ubiquitous nature [30]. Empirical evidence also suggests that the use of mobile apps appears to be a feasible assistive technology intervention for caregivers of PWD [31] and potentially effective in improving a range of psychological outcomes such as reducing levels of burden, anxiety, and depression [32–34].

However, few of the apps presently available in the market have been developed specifically to address the needs of informal caregivers of PWD. A recent review by Castillo et al. [35] found only 16 apps which met their criteria for a focus on dementia care for informal caregivers of PWD, out of which only 3 were supported by some evidence in the literature. In another review, Brown et al. [36] identified only 5 out of 13 apps which had a focus on caregivers and all these apps had limited functions to meet the complex needs of caregivers of PWD. Lastly, a review by Rathnayake et al. [37] revealed a lack of rigorously designed studies with a clear theoretical framework and user-centered approach to app design. Findings from the above studies concurred that the apps reviewed were insufficient to address the multidimensional needs of caregivers of PWD and highlighted the need to develop more user-centered and evidence-based apps [35].

More importantly, none of the apps reviewed are based in Singapore. To the best of our knowledge, there is currently only one mobile app developed to support dementia caregivers in Singapore (i.e., CARA). Key features of the CARA app include (1) helping to locate and enable the safe return of missing PWD, (2) involving and notifying other family members by connecting with them through a connected care circle, (3) providing tailored discounts and privileges for members, and (4) access to a list of solution providers for various needs [38]. This highlights a clear gap in the development and empirical evaluation of mobile-based interventions with culturally sensitive resources for different stages of dementia in Singapore. This study will therefore evaluate the effectiveness of a multi-component mobile-based intervention comprising culturally relevant knowledge and resources aimed at improving mental health outcomes for informal caregivers of PWD in Singapore. We aim to examine differences in levels of depressive and anxiety symptoms, caregiver burden, mental well-being, caregiving self-efficacy, knowledge of dementia, positive aspects of caregiving, and coping strategies before and post-intervention, as well as between the intervention and control groups.

## Methods

### Study design

A pilot two-armed randomized control trial (RCT) design will be adopted to test the effectiveness of the *Kampung Care* app (*Kampung Care* is a local expression of a caring community). Sixty eligible caregivers of PWD will be enrolled in the RCT and randomly allocated to either the intervention or control group. No blinding will be used as participants and study team members need to be aware of which group the participant belongs to in order to start the intervention. Participants in the intervention group will use the app for one month, while those in the control group will be on a waiting list for one month. Outcome measures will be assessed at baseline and one-month after the baseline assessment (post-assessment). Thereafter, qualitative interviews will be conducted with participants from the intervention group to gather feedback on their experience with the app and areas for improvement. The Standard Protocol Items: Recommendations for Interventional Trials (SPIRIT) checklist is provided (see S1 File).

### Inclusion and exclusion criteria

Participants will be included in the study if they: (1) are at least 21 years of age; (2) a Singapore citizen or permanent resident; (3) currently taking care of a PWD; (4) able to read, write, and speak in English (i.e., the language used for the intervention); and (3) proficient in using mobile applications. Due to ethical considerations, caregivers who are pregnant or have vision or hearing problems will be excluded.

### Sample size

Given that this is a pilot RCT with the primary aim of assessing the feasibility and potential effectiveness of the ’Kampung Care’ mobile intervention, we followed the recommendation from a methodological study that a sample size of 25 per intervention arm is required if the main study is designed with 90% power and two-sided 5% significance for an intervention with a small effect size [39]. No formula or software was used in the calculation. With a 1:1 allocation ratio, the required sample size was determined to be 50. As mobile-based intervention studies tend to have high attrition rates, we doubled our preliminary sample size to 100 to ensure there will be a sufficient sample for analysis. However, following the initial recruitment, we found the attrition rate among our target group to be quite low and thus adjusted our final sample to 60 –with 30 participants randomly allocated to the intervention group and waitlist control group respectively. For the in-depth interview, we intend to recruit up to 20 participants from the intervention group. This is from an experiential perspective. However, the final sample will depend on data saturation–the point at which no new information is being observed and collected to form distinct themes.

### Participants

Participants will be referred by collaborating clinicians from the outpatient clinic of the Institute of Mental Health (a tertiary mental health service provider) and a geriatric clinic of a local hospital when they accompany the PWD during outpatient visits. Recruitment flyers may be put up in clinics as posters and/or distributed to clinicians to pass to potential participants interested in the study to contact us. In addition, we will also contact caregivers who have participated in our prior studies. Snowball recruitment will also be used by asking all caregivers with whom we come into contact to refer other potential participants. Collaborating clinicians and caregivers who refer eligible participants to us will be reminded to obtain approval from the potential participant first. Thereafter, the study team will either follow up with the potential participant to obtain their contact details at the clinic or directly contact them via phone call. Public advertisement of the study will be done through social media platforms like Facebook and LinkedIn. Lastly, we will also approach external organisations with a large base of caregivers of PWD to ask for their help in advertising the study online.

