### Study procedure

Once a caregiver agrees to participate, a study team member will schedule a session with them. All sessions will be conducted either online via a video-conferencing platform like Zoom or in-person, based on the caregiver’s preference. After the study team member goes through the informed consent form and obtains the participant’s signed consent, screening will be done using the 4-item version of the Zarit Burden Interview (ZBI) [40]. Caregivers who score 4 and above will be included in the study, while those who score 3 and below will be excluded.

A study team member will assign participants to either the intervention or wait-list control group using block randomisation with a block size of four. An independent statistician not involved in the day-to-day administration of the project will conduct the randomisation by generating a sequence of numbers using the Sealed Envelope online tool on the randomisation website [41]. Allocation concealment is achieved by the ’sealed envelope’ method, in which the envelope contains a random code that must be checked against the randomisation list to determine group information. This is to prevent potential selection bias. Thereafter, the participant will be allocated into a group and complete the baseline assessment. One month later, a study team member will contact the participant to complete the post-assessment. Intervention group participants will also be invited to join a semi-structured interview to share their experience with the app and feedback on areas for improvement. Participants will be disbursed an inconvenience fee through cash or cashless modes of payment on completion of the baseline assessment (SGD25), post-assessment (SGD35), and follow-up interview (SGD30). Please refer to Fig 1 for the schedule of enrolment, intervention, and assessments. The approved study protocol can be found in S2 File.

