### Intervention delivery

The intervention group will be required to use the Kampung Care app for one month. Caregivers will be asked to complete at least two positive reflection journal entries per week (i.e., one in the middle of the week and one at the end of the week) and encouraged to use other app features. However, the actual usage of the app is ultimately dependent on users based on their schedule and interests during the one month. Follow-up calls will be made by a study team member weekly to seek feedback, provide clarification and assistance if needed, and to remind and motivate caregivers to continue app usage. During the call in the second week of app usage, the Patient Health Questionnaire-9 (PHQ-9) will be used to assess users’ mental health to monitor their risk and provide self-help resources if necessary. In the meantime, caregivers in the control group will be placed on a waiting list for one month.

After the end of one month, the post-assessment will be conducted for both groups. Scores from the post-assessment will be compared with that for the baseline to determine the effectiveness of the app. Caregivers’ app usage will also be analysed to examine links between usage patterns and intervention effects. Participants in the control group will also be given access to the app after completing the post-assessment, but they can refuse if they do not want access.

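### Snowball referral, individual open allocation and no limit of one caregiver per PWD allow linked caregivers to be split between arms; any shared app content would bias the difference toward zero by an unknown amount

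*Protocol article*

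**What the plan says.** The Abstract (Methods) describes "60 informal caregivers of PWD recruited via convenience and snowball sampling". The Participants section states the referral route: "Snowball recruitment will also be used by asking all caregivers with whom we come into contact to refer other potential participants". This is one of several routes; the others are clinician referral, flyers, people from the team's prior studies, social media and external organisations.

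Under Inclusion and exclusion criteria, the only requirement tied to the care recipient is "3) currently taking care of a PWD". The exclusions are that "caregivers who are pregnant or have vision or hearing problems will be excluded". Study procedure adds a burden screen (4-item ZBI score of 4 or more). None of these concerns a shared PWD or a link to someone already enrolled.

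On allocation, Study procedure says: "A study team member will assign participants to either the intervention or wait-list control group using block randomisation with a block size of four". Study design says: "No blinding will be used as participants and study team members need to be aware of which group the participant belongs to". Intervention delivery sets when controls officially receive the app: "Participants in the control group will also be given access to the app after completing the post-assessment".

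**The concern.** The referral request goes to every caregiver the team meets, with no exception for people already randomised. App-arm participants are telephoned weekly, so contact continues after allocation. The Background notes that informal carers are usually family members, so two relatives looking after one PWD can both qualify. Each is allocated separately and knows the result.

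Parts of the app can be passed on without a log-in: dementia information, the list of local resources and the idea of the reflection journal. Dementia knowledge and coping are themselves secondary outcomes, so shared content would act directly on what is measured. Any benefit that reaches a control during the waiting month shrinks the contrast between the arms. In a pilot that is meant to gauge feasibility and likely benefit ahead of a main study, the main harm is an effect estimate that is too small. The article describes no step that would reveal this, and the limitations in the Discussion do not mention contamination.

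**Working it through.** **Inputs from the article.** Blocks of four and 1:1 allocation (Study procedure; Sample size). The plan's own size figures reproduce: 2 x 25 = 50 required, and the final 60 gives 60/2 = 30 per arm. The article states no figure for linked pairs, shared PWDs or contamination.

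**1. Chance that a linked pair is split.** A balanced block of four has 6 possible sequences.
- Same block: once the first member is placed, 2 of the other 3 slots belong to the other arm, so P = 2/3 = 0.667.
- Different blocks: P = 1/2 = 0.50.
- Consecutive enrolments, averaged over position in the block: 3/4 x 2/3 + 1/4 x 1/2 = 0.625.
- Two places apart: 2/4 x 2/3 + 2/4 x 1/2 = 0.583.
- Three places apart: 1/4 x 2/3 + 3/4 x 1/2 = 0.542.
- Four or more apart: 0.50.

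If there were three linked pairs (assumed, and treated as independent), the chance that at least one is split lies between 1 - 0.5^3 = 0.875 and 1 - (1/3)^3 = 0.963. Once linked pairs are enrolled, some splitting is the likely result.

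**2. Dilution per exposed control.** Let c be the share of controls who gain the full average app effect. The expected difference is then multiplied by (1 - c).
- One of 30: c = 1/30, a loss of 3.3%.
- Three of 30: c = 10%, a loss of 10%.
- Six of 30: c = 20%, a loss of 20%.

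These are ceilings, provided an exposed control gains no more than the average app effect. If one exposed control gained half of it (assumed), the loss would be 0.5/30 = 1.7%.

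**3. Non-independence.** Let the change scores have variance V and correlation r within a linked pair, with m pairs split and s pairs in the same arm. The variance of the difference in mean change is

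2V/30 + 2rV(s - m)/30^2 = (2V/30) x [1 + r(s - m)/30].

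For positive r, split pairs lower the true variance, so an ANOVA that ignores the link is conservative for them. Same-arm pairs raise it. Because a pair is split with probability of at least 0.50, s does not exceed m on average. Non-independence therefore has no established harmful direction here.

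**The case against.** The strongest reply is that the concern rests partly on silence in a condensed article. The approved study protocol is a supplementary file that is not at hand, and it could hold a household rule or a referral log. That stands as a caveat. But recruitment route, eligibility and unit of allocation are protocol decisions that the article does state, and its eligibility list reads as complete. As stated, these rules open the route.

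It is also fair to say that snowballing is one route among several, that co-enrolled relatives are a possibility and not a documented fact, that controls get official access only after the post-assessment, and that second-hand sharing would not deliver the whole package, such as the weekly calls. These points limit the likely size. Delayed official access does not, however, prevent informal sharing.

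Three stronger readings are tempting, and the article does not support them.
- A reader might convert contamination into lost sample size: 60 x (1 - c)^2 gives about 54, 49 and 38 at c = 5%, 10% and 20%. Those rates are assumed, and the formula gives every exposed control the full app effect. The figures are worst cases. In a pilot sized by a rule of thumb, lost power is also not the main criterion.
- A reader might blame the blocks of four. Simple randomisation would already split half of all linked pairs, and the excess over 0.50 disappears once enrolments are four or more places apart.
- A reader might infer that linked pairs invalidate the ANOVA. For split pairs with positive correlation the error is in the conservative direction.

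**Conclusion.** The point holds as a preventable risk of bias. The stated recruitment, eligibility and allocation rules let linked caregivers, including two carers of one PWD, fall in opposite arms, with probability 0.50 to 0.67 for each linked pair. Shared content would then bias the difference toward zero. It would mask a benefit, not create a false one.

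The size cannot be worked out from the article. What can be said is a ceiling of about 3.3% dilution for each control exposed, assuming 30 controls and no more than the average effect passed on. Whether any such pair exists is unknown, and the full protocol may already contain a limit.

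**What to change.** - For remaining recruitment, add one eligibility line: only one caregiver per PWD may be enrolled.
- For every participant, record the study number of the referring participant and any PWD shared with another participant. For those already enrolled, take this from recruitment records.
- At the control post-assessment, before access is offered, ask whether the participant saw or used the app.
- Add a sensitivity analysis of the primary outcome (CES-D) that keeps only the first-enrolled member of each linked set. Selection then depends on enrolment order and not on allocation. It does not by itself remove exposure of a first-enrolled control by a later app-arm relative, so read it alongside the exposure answers.
- If the full protocol already has such a rule, state it in the article.

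**Cost.** One eligibility line, two log fields, one question and one extra analysis. A few referred caregivers are lost, and the sensitivity analysis is slightly smaller. Trial status gives recruitment from December 2022 to the end of March 2024, so the eligibility line may reach few people. The retrospective link check and the sensitivity analysis remain possible afterwards, as does the exposure question for controls not yet assessed.
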